### 11.1 Study Outcome Measures

#### 11.1.1 Definitions of Malaria Infections

##### **Symptomatic *Plasmodium* Infection**

For diagnostic purposes, a symptomatic *Plasmodium* infection is defined as any type of *Plasmodium* parasitemia observed by blood smear and/or a positive rapid diagnostic test, plus an axillary temperature  $\geq 37.5^{\circ}\text{C}$  or a history of febrile illness in the last 48 hours.

However, for analytical purposes we will use 2 different definitions for symptomatic *Plasmodium* infections: a) any type of *Plasmodium* parasitemia observed by blood smear and/or PCR/LDR diagnostic assay, plus an axillary temperature  $\geq 37.5^{\circ}\text{C}$  or a history of febrile illness in last 48 hours b) a parasite density of  $>5000/\mu\text{L}$  for *P. falciparum* and/or  $>500/\mu\text{L}$  for non-*falciparum*, plus an axillary temperature  $\geq 37.5^{\circ}\text{C}$  or a history of febrile illness in the last 48 hours.

##### **Asymptomatic Blood-stage *Plasmodium* Infection**

An asymptomatic blood-stage *Plasmodium* infection is defined as any type of *Plasmodium* parasitemia observed by blood smear or PCR-LDR confirmation with an axillary body temperature less than  $37.5^{\circ}\text{C}$  and no history of febrile illness in last 48 hours.

#### 11.1.2 Primary Outcome Measures

##### **11.1.2.1 Incidence of clinical *P. falciparum* or *P. vivax* episodes during the 32 weeks of follow-up**

The comparison of the incidence of clinical *P. falciparum* and *P. vivax* episodes between the 2 study arms is a primary objective of the study and will be evaluated by assessing differences in both the incidence of *P. falciparum* *P. vivax* episodes over 32 weeks of follow-up and the incidence of first or only *P. falciparum* / *P. vivax* episodes

Children will be considered 'at risk' until they reached the endpoint of interest, withdrew, were lost to follow-up or completed the study. For clinical and molecular endpoints children were censored on the last day before the first of two consecutively missed active follow-up visits

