## 4 STUDY DESIGN

In this study 500-600 children aged 5-10 years will be screened, enrolled and randomized to 2 arms of a longitudinal cohort study. The randomized arms will comprise:

- 250-300 children pre-treated with 3 days Chloroquine (CQ), 4 weeks Primaquine (PQ) and 3 days Coartem (CO)
- 250-300 children pre-treated with 3 days Chloroquine (CQ), 4 weeks Placebo (PL) and 3 days Coartem (CO)

At enrolment all eligible children aged 5-10 years in the study area will be screened for Glucose-6-Phosphate Dehydrogenase deficiency (G-6-PD) and the presence of severe anaemia or malnutrition. Children with less than 60% G-6-PD activity, haemoglobin <5g/dl or severe malnutrition (weight-for-age nutritional Z score [WAZ] <60th percentile) will be excluded from the study. All other children will be randomized to the two treatment arms of the study.

Drug treatment will commence at enrolment. All children will receive CQ on days 1-3. Children will also receive either PQ (0.5 mg/kg) or placebo on days 1-5, 8-12, 15-19 and 22-26 (i.e. Monday to Friday for 4 weeks). During the third week of drug treatment all children will receive CO on days 15-17 (according to national treatment guidelines). Children will be actively monitored for side effects including measurement of haemoglobin levels at days 1, 8, 15 and 22.

Following completion of treatment, children will undergo a clinical examination and a 10 mL venous blood sample will be collected on day 29 (i.e. 26 days after their last dose of CQ, 12 days after their last dose of CO and 3 days after their last dose of PQ or PL).

Subsequently, all enrolled children will be followed using 2-weekly active and continuous passive case detection at a local health centre for 8 months (Week 2-32). Active follow-up consists of morbidity surveillance visits to monitor clinical malaria illness not reported to a health facility, as well as blood sampling for the detection of asymptomatic malaria. These visits will include collection of a medical history of the preceding 2 weeks to determine incidence of malarial infections and bed net usage, a physical examination, measurement of axillary temperature. A 250µl finger prick blood sample will be collected every 2 weeks for the first 12 weeks and 4 weekly thereafter, i.e. weeks 2, 4, 6, 8, 10, 12, 16, 20, 24, 28 and 32.

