All blood samples will be assessed for the presence, type, and number of malarial infections (by light microscopy and PCR) and Hb levels. The 10 mL venous blood samples will also be used for the assessment of humoral and cellular immune responses to *Plasmodium* infections (Aim 2). DNA

extracted from venous blood samples and the finger-prick blood samples collected during follow-up will be assessed in molecular parasitology studies (Aim 1).

During the entire study period, a passive case detection system will be maintained at the local Health Centre. Every participating child that presents at the health centre with a febrile illness will be clinically assessed and have a finger prick blood sample taken for determination of malaria infections by a Rapid Diagnostic Test (RDT), two blood slides for microscopy confirmation and HemoCue® for Hb concentration. In accordance with the new national treatment guidelines, only children with a positive RDT will receive Coartem treatment from the attending field Nurse. All the data collected will be recorded in the morbidity forms and the health book of each participating child to be reviewed by the study clinician.

Over the 9-month study duration, each participant will have 38 contacts with the study team (1 for enrolment/screening, 20 for supervision of drug administration, 1 baseline time-points (after drug treatment), 16 active follow-up visits) and will be asked to contribute one 10 mL venous blood sample at the baseline visit and 12 finger prick blood samples (250µL) (see Study Schedule Diagram, Appendix I.) Additional finger prick blood samples may be collected at the time of febrile illness during morbidity follow-ups and passive case detection.

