### **6.1.6 Active Surveillance**

Following the collection of the 10 mL venous blood sample the study team will contact each participating child every 2 weeks and conduct a brief clinical evaluation of each child during a clinic held at the participant's school.

The study team will specifically perform the following tasks:

- Record axillary body temperature of the child,
- Assess the child for symptoms of malaria infection,
- Determine if the child is suffering from symptomatic malaria (or clinical signs and symptoms of anemia),
- Check the fingers of the child for redness or signs of irritation from lancet finger punctures.
- Record information relating to:
  - history of bed net use for the study participant since the previous visit,
  - participant's history of illness since previous visit,
  - history of malaria treatment for the study participant since previous visit,
- Check the child's health records booklet for recent health center visits and record applicable information,
- Inform the child's teacher and school administration of the next follow-up visit and the reasons for the tasks to be performed.

If the participant is judged to be suffering from malaria illness at the time of the morbidity surveillance visit, finger prick blood samples will be collected for determination of parasitaemia and Hb levels. The presence of malarial parasites will be diagnosed in the field using RDT. For children excluded from undertaking RDT tests, blood smears will be read overnight for malaria diagnosis. Upon positive RDT or positive blood smear or in the case of moderate-to-severe anemia (Hb <8.0 g/dL) the study team will initiate treatment as per national standard treatment guidelines.

In the first 12 weeks of follow-up, a 250 µL finger prick blood sample will be collected at 2 weekly morbidity surveillance visits. Thereafter a finger prick sample will be collected every 4 weeks only.

The blood samples will be used to produce blood smears for assessing blood-stage malaria infection, type of *Plasmodium* parasite(s), and level of parasitaemia. A portion of this sample will be collected in a microtainer for further analysis (i.e., PCR/LDR-based diagnosis of malaria infection and for immunological studies). A few drops of blood will be collected on a filter paper for detection of gametocytes.

In total the team will conduct 16 follow-up visits that will include 11 finger prick blood sampling time points.

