### **7.6 Criteria for Discontinuation or Withdrawal of a Subject**

Parents and/or guardians may withdraw their child at any time from the participations in this study.

A participating child will be discontinued from the study if 1 of the following criteria are fulfilled:

- the participant moves away from the selected study villages for a period longer than 2 months
- the participant develops a chronic illness that impedes continuation in study. Children developing severe anemia (Hb <5 g/dL) or severe malnutrition (WAZ <60%) may be discontinued by the study physician if medically indicated.

Participants who are discontinued because of acute or chronic illness may continue to consult the study team nurses during 2 weekly morbidity visits for health problems, if they wish to do so.

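### The two-missed-visits censoring rule has no re-entry, so it drops observed follow-up from the total-episode analysis, and after week 12 it counts active visits instead of blood samples for infection endpoints

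*Protocol*

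**What the plan says.** Section 11.1.2.1 of the Protocol sets the time at risk. The rule opens with "For clinical and molecular endpoints" and continues: "children were censored on the last day before the first of two consecutively missed active follow-up visits". No re-entry is described. Section 11.3.1.1 analyses the total number of *P. falciparum* episodes over 32 weeks, and the first or only episode, by Poisson regression, with exposure taken from the risk time defined earlier. Sections 11.1.2.2, 11.1.2.3 and 11.3.1.3 add no separate rule for missed blood samples.

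Absence ends participation only if "the participant moves away from the selected study villages for a period longer than 2 months" (section 7.6). Section 4 plans "2-weekly active and continuous passive case detection at a local health centre for 8 months" and adds: "During the entire study period, a passive case detection system will be maintained at the local Health Centre". At each attended visit the team also takes the illness and treatment history since the previous visit and checks the health booklet (section 6.1.6).

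On sampling, section 6.1.6 says "In total the team will conduct 16 follow-up visits that will include 11 finger prick blood sampling time points". Section 4 places these samples at "weeks 2, 4, 6, 8, 10, 12, 16, 20, 24, 28 and 32". After week 12, "Thereafter a finger prick sample will be collected every 4 weeks only".

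**The concern.** There are two separate problems.

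- **Total clinical episodes.** A Poisson model with an exposure offset can leave out an unobserved interval and carry on. Ending risk time at the first double miss instead discards episodes and time that the study goes on to observe in a child who is still enrolled.
- **First-infection endpoints.** What matters is when blood was last examined. Through week 12, active visits and routine samples coincide. Afterwards they do not, so a rule that counts visits is too strict for some gaps in sampling and too lenient for others.

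At stake are the precision of a primary outcome and consistent risk time for the infection outcomes.

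**Working it through.** **Schedule.** Visits at weeks 2, 4, ..., 32 number 32/2 = 16. Six samples through week 12 plus five at weeks 16, 20, 24, 28 and 32 make 11. Both match section 6.1.6. Visits at weeks 14, 18, 22, 26 and 30 carry no routine sample.

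**One child.** Missing weeks 4 and 6 and returning at week 8, the child is censored the day before week 4. Lost: 32 − 4 = 28 weeks, of which 32 − 8 = 24 come after return.

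**Whole cohort.** The Protocol gives no miss rate, so take an assumed probability p of missing each visit, independently, with q = 1 − p.

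- Let a(n) be the probability of no two consecutive misses in n visits: a(0) = a(1) = 1, a(n) = q·a(n−1) + p·q·a(n−2). The share censored is 1 − a(16).
- The first double miss starts at visit k with probability P(1) = p², and P(k) = a(k−2)·q·p² for k = 2 to 15. Risk time is then 14k − 1 of 224 days. Share kept = 1 − Σ P(k)·(225 − 14k)/224.
- Gap-only exclusion removes the time from the first missed visit of each run of two or more misses to the next attended visit (or week 32).

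All 2^16 = 65,536 attendance patterns were enumerated:

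| Assumed p | Censored early | Kept, rule as written | Kept, gap only |
|---|---|---|---|
| 5% | 4% | 98% | 99.6% |
| 10% | 13% | 93% | 98% |
| 15% | 26% | 86% | 96% |
| 20% | 41% | 77% | 93% |

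About 93% of the censored children attend again, and on average 6 to 7 attended visits per censored child fall after censoring.

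**Precision.** With a constant episode rate, expected episodes scale with person-time and the standard error of the log rate ratio with 1/√(share kept). At p = 10% this is 1/√0.93 = 1.04 under the rule and 1/√0.98 = 1.01 with gap-only exclusion. At p = 20% it is 1/√0.77 = 1.14 against 1/√0.93 = 1.04.

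**Sampling mismatch after week 12 (needs no assumed rate).**

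- Missed weeks 14 and 16: one sample lost, 8 weeks between samples (12 to 20). Censored.
- Missed week 16 only: the same sample lost, the same 8 weeks. Not censored.
- Missed weeks 16 and 20, attended 14, 18 and 22: two samples lost, 12 weeks between samples (12 to 24). Not censored.
- Missed weeks 16, 20, 24, 28 and 32, attended the visits between: 32 − 12 = 20 weeks without a routine sample. Never censored.
- Missed weeks 16 and 18: censored the day before week 16, so almost 4 weeks after the week 12 sample count as infection-free.

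At p = 5%, 10%, 15% and 20%, about 1%, 3%, 5% and 7% of children miss two or more consecutive sampling visits from week 12 on and are never censored.

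**The case against.** The rule is stated in advance, applies equally to both arms and is conventional for first-event outcomes: once a first event may lie in an unobserved gap, a later one cannot be called the first. That stands, and it confines the lost-episode point to the total count. For first-or-only clinical episodes the rule is defensible.

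A reader might infer that the Protocol declares exclusion to be permanent. It does not say so. That is the plain meaning of censoring with no re-entry given, and an SAP not shown here might allow re-entry. Section 6.1.5.1 describes follow-up status as updated every 2 weeks, but says nothing about returning to the risk set.

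A reader might also infer that the infection rule is wrong throughout. It is not: through week 12 every active visit is a sampling visit. Many first *P. vivax* infections should fall in that window. With the prior medians in section 11.2.1 (54 days by PCR, 118 by light microscopy) and a constant hazard, the share by day 84 is 1 − 2^(−84/54) = 66% and 1 − 2^(−84/118) = 39%.

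Nor do a child missing week 16 only and a child missing weeks 14 and 16 carry the same information. Their routine samples match, but the first was examined at week 14, with a treatment history that matters because section 11.1.2.3 censors at first antimalarial treatment. Extra samples are also taken at illness visits.

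Finally, section 11.2.1 adds 25% for loss to follow-up to the infection sample size. That may absorb some of the loss, but is no reason to discard observed data.

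**Conclusion.** The point holds in this limited form. For the total number of clinical episodes, the rule as written removes follow-up that the study observes. The loss is small at a 5% miss rate (about 2% of person-time, against 0.4% for gap-only exclusion) and material at 20% (about 23% against 7%). These figures rest on assumed, independent misses; clustered absence would change them.

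A reader might infer a biased treatment comparison. The documents do not support that: section 6.1.4 blinds participants and study teams with placebo, and bias would need missed visits to be related to arm or risk. What is shown is a loss of precision.

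For infection endpoints after week 12, the trigger does not track missed samples. This follows from the visit schedule alone. It is a worthwhile, inexpensive correction and does not threaten the trial's validity.

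**What to change.** Amend section 11.1.2.1 as follows.

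- **Total number of clinical episodes:** exclude only the gap covered by consecutive missed active visits, and resume risk time at the next attended visit.
- **First-infection endpoints (incidence and time to event):** keep censoring, but trigger it by consecutive missed scheduled blood samples. Date it at the last blood sample taken, counting samples from illness visits.
- **First-or-only clinical episodes:** the existing rule may stay.

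If re-entry was always intended for the total count, one sentence saying so is enough for that part.

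No new data are needed; only the person-time derivation changes. The small downside is that re-entry assumes returning children resemble those who stayed, so report the analysis under the existing rule as a sensitivity analysis.

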#### **11.1.2.2 Incidence of first or only *P. falciparum* or *P. vivax* infection**

The analyses of difference in incidence of first or only *P. falciparum* / *P. vivax* infections will follow that approach for analyses of first or only *P. falciparum* / *P. vivax* episodes, with the difference that children will be considered at risk only until they experience the first *P. falciparum* / *P. vivax* infection.

#### **11.1.2.3 Time to first *P. falciparum* / *P. vivax* infection**

For the analyses of time to first *P. falciparum* / *P. vivax* infection children will be at risk until they either experience a *P. falciparum* / *P. vivax* infection or they are treated with antimalarial drug for another malarial infection. At the time of the first antimalarial treatment, the child will be censored from analysis.

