## 2.3 Potential Risks and Benefits

### 2.3.1 Potential Risks

This study uses two types of anti-malarial drugs to remove blood and liver stages of malarial infections in the study children. A 3 day course of Coartem (artemeter-lumefantrine (AL)) will be used to clear blood stages in both pre-treatment arms while primaquine (PQ) will be used to eradicate liver stages in the pre-erythrocytic pre-treatment arm. In addition, a 3-day course of chloroquine will be administered to all study children at the beginning of drug treatment to assist with the clearance of blood-stages and achieve effective clearance of hypnozoites, together with primaquine, in the pre-erythrocytic arm. AL and chloroquine are well tolerated in PNG children and the schedule and dosage used in the trial correspond to the national standard treatment guidelines. Primaquine has been extensively used in the past in PNG as a gametocidal drug as well as in a short course for eradication of *P. vivax* liver stages but is rarely used today. Primaquine is generally well tolerated and has been used for the eradication of *P. vivax* liver stages in children as young as 3 months in trials of mass drug administration for the eradication of malaria in Vanuatu (13). In addition, in the recent cohort conducted in Ilaaita 150 children 1-5 years were treated with 14 days of primaquine. Detailed monitoring of side effects revealed that drug was safe and very well tolerated ([name] et al in prep). As the drug may lead to gastro-intestinal side effects (nausea etc) if not taken with food, we will give the drug with a bit of soft food prior to drug administration and actively monitor side effects during the entire duration of treatment. The use of primaquine is contraindicated in people with G-6-PD deficiency where treatment with 8-aminoquinolines may induce hemolytic anaemia. We will therefore screen all eligible study children for the presence of G-6-PD deficiency and children with less than 60% G-6-PD activity will be excluded from the study. Children with mild G-6-PD deficiency (60-80% activity) will be randomized to the two arms of the study.

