#### **6.2.1.2 Sample Separation and DNA Extraction**

All 250 $\mu$ L finger stick blood sample collected will be separated into plasma and cell pellets and frozen and stored separately. Blood from 10 mL venous blood draw will be separated into plasma, peripheral blood mononuclear cells (PBMCs) and red blood cell (RBC) fractions using standard protocols. Fractions from 10 mL venous samples will be aliquoted and frozen as required. Detailed protocol for sample separation will be described in the laboratory SOPs.

Deoxyribonucleic acid extraction will be performed using the QIAmp 96 blood extraction protocol (QIAGEN). This approach enables DNA extraction from 192 samples in 2 to 3 hours and has been used successfully to PCR amplify both human- and malaria parasite-specific amplicons for genotypic and species specific diagnostic assays, respectively.(15)(16) Because DNA extraction methodologies are based upon starting with whole blood, preliminary protease treatment will lyse leukocytes, erythrocytes and *Plasmodium* parasites. Therefore, purified genomic DNA contains a mixture of human and parasite DNA. The protocol for DNA extraction will be in accordance with the procedures set forth in the standard operating procedures (SOPs).

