#### **6.2.1.3 Diagnosis of Malaria Infection by Polymerase Chain Reaction/Ligase Detection Reaction**

As each individual's genomic DNA preparation contains human and parasite DNA, blood samples can be used directly to perform species-specific PCR/LDR-based diagnosis of *Plasmodium* infection.(16). The protocol for the PCR/LDR-based diagnosis of malaria infection will be in accordance with the procedures set forth in the SOPs. In all samples positive by PCR/LDR we will determine the presence of *P. falciparum* and *P. vivax* gametocytes using a novel reverse transcriptase-PCR assay using dried filter paper blood spots.

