## 8 ASSESSMENT OF OUTCOME MEASURES

### 8.1 Specification of the Appropriate Outcome Measures

#### 8.1.1 Primary Outcome Measures

- Time-to-first *P. vivax* and *P. falciparum* infections by LM and PCR in the 32 week follow-up period. (Aim 1)
- Incidence of first or only *P. vivax* and *P. falciparum* infection by LM and PCR during the 32 weeks of follow-up. (Aim 1)
- Incidence of clinical *P. falciparum* and *P. vivax* episodes during the 32 weeks of follow-up. (Aim 1 & 2)
- Incidence of first or only clinical *P. falciparum* and *P. vivax* episode during the 32 weeks of follow-up. (Aim 1 & 2)

Clinical *P. falciparum* and *P. vivax* malaria is defined as an axillary temperature  $\geq 37.5^{\circ}$  (or a history of fever lasting more than 2 days in duration) together with concurrent *P. falciparum* and/or *P. vivax* parasitaemia.

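### The time-to-first-infection endpoint has no rule for when an infection is new, so parasites persisting to week 2 could be scored more often in the placebo arm and partly mimic a primaquine effect

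*Protocol*

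**What the plan says.** Section 8.1.1 lists, among the primary outcomes, time to first *P. vivax* and *P. falciparum* "infections by LM and PCR in the 32 week follow-up period. (Aim 1"), and the incidence of first or only infection by the same methods.

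Section 11.1.2.3 sets the risk period: for time to first "infection children will be at risk until they either experience a" *P. falciparum* or *P. vivax* infection, or receive antimalarial treatment for another malaria infection. It adds: "At the time of the first antimalarial treatment, the child will be censored from analysis". Section 11.1.2.2 likewise ends risk at the first infection. Section 11.1.1 defines an asymptomatic infection as any type of "parasitemia observed by blood smear or PCR-LDR confirmation with an axillary body temperature less than" 37.5°C and no recent fever. It sets no condition on parasite stage or genotype.

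On the assay, Section 6.2.1.2 notes that "purified genomic DNA contains a mixture of human and parasite DNA", because whole blood is extracted. Stage is found by a separate test. Section 6.2.1.3 says: "In all samples positive by PCR/LDR we will determine the presence of" gametocytes by reverse-transcriptase PCR. Section 6.2.1.5 plans genotyping of every PCR-positive *P. falciparum* and *P. vivax* infection. Section 3 assigns that genotyping to the infection-dynamics objective, not to the first-infection endpoint.

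On treatment, both arms receive chloroquine and Coartem, and one also receives primaquine to day 26 (Section 4). Section 2.3.1 states: "Primaquine has been extensively used in the past in PNG as a gametocidal drug". The post-treatment baseline (Week 0) sample is taken on day 29, "12 days after their last dose of CO and 3 days after their last dose of PQ or PL".

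**The concern.** The endpoint is meant to measure re-infection or relapse after clearance, and Section 11.2.1 sizes the trial on new *P. vivax* infections. The operational rule does not carry that idea through. A child with parasites at Week 0 and the same clone at week 2 would be recorded as having a first infection at 2 weeks.

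If this happened equally in both arms, it would only add noise. It may not be equal, because one arm alone receives the drug that the protocol describes as acting on gametocytes. PCR on whole-blood DNA does not by itself show whether a positive is a new asexual infection or residual gametocytes. The protocol expects sexual stages after treatment, since studying them following radical cure is a secondary objective (Section 3).

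For *P. falciparum*, the stake is an apparent primaquine effect on an outcome for which the protocol states no liver-stage objective. For *P. vivax*, any such leftover would add to the difference attributed to long-lasting liver stages, which is the first primary objective.

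Adjusting for infection status before treatment (Section 11.3.1.3) does not solve this. The imbalance would arise after randomisation, from clearance that differs by arm.

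**Working it through.** **Does any passage define a new infection?** Sections 8.1.1, 11.1.1 and 11.1.2.1 to 11.1.2.3 state when risk ends. None requires a negative Week-0 sample, a new genotype or asexual stages. Section 6.1.5 ties testing at Week 0 to symptoms and treatment to a positive test or Hb below 8.0 g/dL, so a child who is PCR-positive without symptoms or anaemia can go on into follow-up.

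**How long must a leftover last?** Week 2 is day 29 + 14 = day 43. The last Coartem dose is on day 17, the last chloroquine dose on day 3 and the last primaquine dose on day 26. To be scored, a leftover must be detectable 43 − 17 = 26 days after Coartem, 40 days after chloroquine and, in the primaquine arm, 17 days after primaquine.

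**The plan's own figure.** Section 11.2.1 gives 200 per arm and 90% power for a hazard ratio of 0.70 by PCR, from a 54-day median. With exponential times over 224 days, the cumulative risks are 1 − exp(−ln 2 × 224/54) = 0.944 under placebo and 1 − exp(−0.7 × ln 2 × 224/54) = 0.866 under primaquine. Expected events are 200 × (0.944 + 0.866) = 362. The Schoenfeld formula at two-sided 5% (assumed, as alpha is not stated) gives √(362/4) × 0.357 − 1.96 = 1.43, or 92.4% power. This is close to the stated 90%, but only if the 50% bednet adjustment is ignored. With the median halved as written (27 days) power is 94.4%, and with it doubled (108 days) 84.6%. The point below does not depend on which was meant.

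**Effect of carry-over on the week-2 risk.** With carry-over *x*, the placebo risk at week 2 becomes *x* + (1 − *x*) × *p*.
- 54-day median: *p* = 1 − exp(−ln 2 × 14/54) = 0.164. With *x* = 0.05 it becomes 0.05 + 0.95 × 0.164 = 0.206.
- 30% infected by week 32: *p* = 1 − 0.70^(14/224) = 0.022. With *x* = 0.05 it becomes 0.05 + 0.95 × 0.022 = 0.071.

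The same leftover matters far more when true infections are rare.

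**Effect on the hazard ratio.** Simulated trials: 250 per arm, exponential times, sampling at weeks 2, 4, 6, 8, 10, 12, 16, 20, 24, 28 and 32, true hazard ratio 1, and carry-over in the placebo arm only, scored at week 2.

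| Placebo carry-over (assumed) | 54-day median: apparent HR (rejection) | 30% infected by week 32 (assumed): apparent HR (rejection) |
|---|---|---|
| 2% | 0.98 (about 6%) | 0.93 (about 7%) |
| 5% | 0.95 (about 8%) | 0.86 (about 16%) |
| 10% | 0.89 (about 19%) | 0.74 (about 50%) |

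Repeat runs agreed to about 0.02 in the hazard ratio and about 3 points in the rejection rate.

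**Bounds, at 200 per arm and a 54-day median:**
- 10% carry-over in both arms: hazard ratio about 1.0, so no false effect.
- 10% under placebo against 5% under primaquine: about 0.95, with rejection about 8%.
- True hazard ratio 0.70 with 10% placebo-only carry-over: appears as 0.64.
- True hazard ratio 0.70 with 10% in both arms: appears as about 0.72.
- Carried-over positives removed under the null: hazard ratio returns to 1.00, with rejection about 5%.

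**The case against.** Four objections have force.

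- **The protocol is silent on entry to the risk set.** A reader might infer that it deliberately puts every child at risk whatever the Week-0 result. It does not say so, and a later analysis plan could settle entry. What stands against this is that the protocol itself writes the end-of-risk rule for a primary outcome, and that rule counts any positive.
- **The imbalance is not documented.** No section says that chloroquine or Coartem leaves gametocytes, in which species, or for how long. Both arms receive both drugs, which limits residual asexual parasites, and a leftover must last about 26 days after Coartem. This stands in full, and it is weightiest for *P. vivax*.
- **There are partial safeguards.** Smear results are expressed as asexual parasites (Section 6.2.1.1), and microscopy is listed beside PCR. Analyses above density cut-offs are planned (Sections 11.3.1.2 and 11.3.1.3) and should be less sensitive to low-density residue. The gametocyte route therefore bears mainly on PCR.
- **The clearest case has an uncertain rank.** *P. falciparum* infection is primary in Section 8.1.1 but is called secondary in Section 11.2.2.

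A reader might also want to redefine the primary endpoint so that Week-0 positives are excluded or enter late. The documents do not support that. It conditions on a result obtained after randomisation that may differ by arm. A *P. vivax* positive at Week 0 under placebo could also be an early relapse, which is the effect under study.

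**Conclusion.** The point holds as a gap in the endpoint rule. A persisting infection would count as a first infection, only one arm receives the drug called gametocidal, and no planned result is used to separate leftover from new. The direction of a possible bias is clear for *P. falciparum* by PCR and only possible for *P. vivax*.

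The size rests on carry-over rates that the protocol does not give. At the protocol's 54-day *P. vivax* median, 2% to 5% placebo-only carry-over moves a null hazard ratio to 0.98 to 0.95, which is small. At 10% it is about 0.89, with about 19% false rejection.

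The figures of 0.74 and about 50% should not be read as what to expect. They need 10% carry-over confined to placebo and only 30% of children infected by week 32, and both are assumptions. Nor do the documents support inferring that an observed primaquine effect would be false. Equal carry-over produces none, and relapse from existing liver stages is a genuine *P. vivax* effect.

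**What to change.** Keep the all-children analysis as primary. Add to Sections 11.1.2.2 and 11.1.2.3 a pre-specified new-infection sensitivity analysis:

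- ***P. falciparum*:** a positive counts only if it carries a genotype absent from the child's Week-0 sample. A positive with only the Week-0 genotype and gametocytes is not an event.
- ***P. vivax*:** a child PCR-positive at Week 0 enters the risk set after the first negative sample. There is no genotype exclusion, because a relapse may carry the old genotype. State in the report that this may remove early relapses and so bias towards no effect.
- **Reporting:** give Week-0 PCR and gametocyte positivity by species and arm, which shows directly whether carry-over is present and unequal.
- **Rank:** reconcile Sections 8.1.1 and 11.2.2 on whether *P. falciparum* infection is primary or secondary.

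The cost is wording. PCR on all samples, genotyping of PCR-positives and the gametocyte assay are already planned. If 10% of children dropped out of the sensitivity analysis (180 instead of 200 per arm, 54-day median, hazard ratio 0.70), power would fall from 92.4% to 89.6%.

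The downsides are some lost early risk time, missed re-infections with the same genotype, and conditioning on a post-randomisation result. The last is why this analysis stands beside the primary one and does not replace it.
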